## 3-month follow-up

Patient characteristics such as age, sex, BMI, ASA and Charnley class will be used in this study. Apart from whether or not the patient did discharge on DOS and his/her experience from the routine (evaluated by a phone the day after surgery), at 3-month post-surgery the following parameters will also be evaluated:

- Any additional appointments to the outpatient department
- Any complications at the 3 month doctor's appointment
- 30-day adverse events and/or readmission for any cause
- 90-day adverse events and/or readmission for any cause

## Patient information

This is an observational study with the aim to document a routine practice. I.e., the patients will be well informed of the same-day surgery routine, but not asked to participate. The reason is, without the risk of bias, to be able to thoroughly evaluate and perhaps improve the routine in any way.

This study gives us the opportunity to observe and analyse an authentic scenario, as it would e.g. be incorrect only to include the most positive individuals.

# Data analysis

## Statistics

Since the same-day surgery routine has become standard practice and that this observational study is conducted to demonstrate just that, no comparative analyses are planned. Only if unexpected failures will be observed, retrospectively such a comparison will be conducted. (If so, a new retrospective case control study would then be needed.)

Descriptive data will be presented as unadjusted means with standard deviations, medians with range, or as proportions (%).

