## Summary

Fast-track/rapid recovery/Enhanced Recovery After Surgery (ERAS) programs have shown to be proven both safe and effective in joint replacement surgery (JRS), to the degree where same-day surgery have been tested in selected cases. A transition of the minor partial knee replacement (PKR) procedure, compared with the alternative and more commonly used total knee replacement (TKR) for knee osteoarthritis (OA), into a same-day regime seems reasonable. Especially as PKR is reported to have lower risk of short-term complications than does TKR.

The aim of this study is to assess efficacy, patient satisfaction and safety outcome measures for PKR when using a same-day surgery protocol in a Swedish healthcare context where ERAS programs for JRS nowadays are considered common ground.

With no preselection of patients, all PKR cases by one high-volume surgeon will chronologically be scheduled as the first morning case during one consecutive year, and thereby be included in this observational study. In order for discharge, strict post-surgery criteria will have to be met. Patient characteristics will be documented and at a 3-month follow-up, percentages of discharge on day of surgery (DOS), patient satisfaction, adverse events (AEs) and readmissions for any cause will be evaluated.

The thesis is that the same-day surgery will be both feasible and safe as the general conception in the medical team prior to this study has been that the PKR patients, everything else equal, above all are more confident with their knee post-surgery than those that have had a TKR procedure done. As the protocol has become standard practice, the aim of this study will be to observe, document, and analyse the overall positive effects we believe this new routine has achieved.

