## Secondary aims

Secondary aims of this study will be to assess efficacy measures such as who and how many will be discharged on DOS, and what burden will instead be allocated to the out-patient department.

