# Patients and methods

## Study design

### *Cohort study – Level of evidence, 2*

This observational study will be conducted at Trelleborg hospital, a public hospital in Region Skåne, a county council in the south of Sweden, performing around 1.500 JRSs each year. The efficacy and safety aspects of the same-day surgery protocol to be assessed is in fact only a slight modification of an existing ERAS protocol that has been used for years at the department.

To best evaluate these measures, the study is pragmatically design as no patient-selection will be done prior to surgery. I.e., all patients, regardless of any medical history, considered for a PKR procedure will also be informed prior to surgery by the multidisciplinary team (nurse, surgeon, anaesthesiologist, and physiotherapist) that if the surgery is to be scheduled in the morning, he/she will then follow a same-day surgery protocol and will likely be discharged to home later the same day.

The actual “recruitment” will be done in the following manner: All of one high-volume surgeon’s first morning cases during one consecutive year will be dedicated to a PKR patient, and thereby also included in this cohort study. The slots will filled continuously as the patients are put up for surgery. When all slots have been occupied within one week any additional PKR cases will be assigned to surgery later in the day in the same week, as will all the TKRs and the THRs this year, and consequently not taking part in the study. (It must be emphasized that, for the fairness of all patients, the operation scheduling will be put

together on a weekly bases, in a strict chronological order, by a team of nurses and without any insight of the surgeon in question.)

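### A comparison is made only if results disappoint, and the uncontrolled cohort cannot support the effect wording in the aims

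*Protocol*

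**What the plan says.** The Statistics section of the protocol states that "no comparative analyses are planned" and goes on: "Only if unexpected failures will be observed, retrospectively such a comparison will be conducted". It adds in brackets that "a new retrospective case control study would then be needed". The planned analysis is descriptive: means, medians and proportions.

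The Summary says that the study will "observe, document, and analyse the overall positive effects we believe this new routine has achieved". The Secondary aims include finding out "what burden will instead be allocated to the out-patient department".

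Every enrolled patient is a first morning case of one surgeon and follows the same-day routine (Study design; Inclusion criteria). Once the week's morning slots are full, "any additional PKR cases will be assigned to surgery later in the day in the same week"; these patients are outside the study.

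**The concern.** Two things do not fit together.

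First, the decision to compare is taken after the results are known and in one direction only. A favourable cohort is reported with nothing beside it. An unfavourable one leads to a retrospective study. The dividing line is not stated.

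Second, the Summary speaks of effects that the routine has achieved, and the secondary aim speaks of burden that is placed elsewhere *instead*. Both are contrasts with another way of organising care, and the plan contains no such contrast.

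At stake is the conclusion of the paper. A report that follows the current text could credit the routine with benefit on uncompared data, while the routine is compared with an alternative only if it disappoints.

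**Working it through.** The protocol gives no sample size, target rate, margin or trigger, so there is no planned figure to reproduce. The check is mainly a reading of the sections together, with two small illustrations on assumed inputs.

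**1. Is the trigger defined?** No. The phrase about failures appears only in Statistics. The 3-month follow-up section lists adverse events and readmissions at 30 and 90 days, complications and additional appointments. It does not say which of these counts as a failure, or how many make an unexpected result. The published same-day discharge rates in Background (85%, 90%, 94%) are not set as benchmarks.

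**2. Who would judge it?** Data management gives the compilation and statistical treatment of the data to the clinical investigator. Disclosures equates the investigator with the surgeon. Reports and publication gives the same person the final form of the report. No one else is named, so in practice the judgement falls to the operator whose results are assessed. This is an inference; the protocol does not assign the decision explicitly.

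**3. Does the rule bias this cohort's own proportions?** No. Let X be the number of events in n patients, p the true rate and T the event that the trigger is met. The proportion X/n is reported whether or not T occurs, so

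P(T) × E[X/n | T] + P(not T) × E[X/n | not T] = E[X/n] = p.

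The rule decides only whether a further study exists.

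**4. How much depends on the missing threshold?** Suppose a comparison follows when at least c failures occur. The chance that none follows is P(X < c) = Σ C(n,k) p^k (1−p)^(n−k), summed over k = 0 to c−1. For example, with n = 50, p = 10% and c = 1 it is 0.9^50 = 0.5%. All values of n, p and c are assumptions.

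| n | p | c = 1 | c = 3 | c = 5 |
|---|---|---|---|---|
| 25 | 5% | 27.7% | 87.3% | 99.3% |
| 25 | 10% | 7.2% | 53.7% | 90.2% |
| 50 | 5% | 7.7% | 54.1% | 89.6% |
| 50 | 10% | 0.5% | 11.2% | 43.1% |
| 100 | 5% | 0.6% | 11.8% | 43.6% |
| 100 | 10% | about 0% | 0.2% | 2.4% |

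For the same true rate, whether a comparison is made can turn almost entirely on a number that the protocol leaves open.

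**5. What would a good result show alone?** With zero events the exact two-sided 95% upper limit is 1 − 0.025^(1/n). For n = 25, 50 and 105, which are sizes of earlier series cited in Background, it is 13.7%, 7.1% and 3.5%. Even an event-free cohort of such a size leaves a range of event rates open.

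**6. Can the design estimate an effect or a shift?** An effect of the routine is a difference between outcomes under it and outcomes without it. Only the first term is observed. In the same way, the count of additional outpatient appointments in the 3-month follow-up section describes use within the cohort. Without a reference count it cannot show that work has moved from the ward to the outpatient department.

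**The case against.** The strongest reply is that the study is descriptive by design and says so. The primary aim is to assess safety outcomes, Patient information speaks of documenting a routine, and a single cohort may properly report adverse events, readmissions and same-day discharge as proportions. The comparison is described as a new study and so lies outside this one. The word *instead* in the secondary aim becomes a plain count in the follow-up section, and the clearest effect wording stands only in the Summary.

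Most of this stands. The descriptive design is not the fault. What remains is an undefined, one-directional trigger written into Statistics, and wording in the Summary and Secondary aims that goes beyond description.

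Three stronger readings are tempting, and the document does not support them.

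- *The results are biased whether or not the trigger is met.* Cohorts sorted by their own result will always show a higher mean in one group and a lower mean in the other. Both are reported here, so the proportion is unbiased overall (step 3).
- *The heading "Level of evidence, 2" promises a controlled study.* The protocol does not define the scale, so nothing can rest on that label.
- *A ready concurrent control group is being thrown away.* The later-in-day cases have the same surgeon and are scheduled by nurses in chronological order. But their number is unknown and could be very small, their discharge pathway is not described, and any contrast would mix the routine with time of day. Including them is an option, not a requirement.

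**Conclusion.** The point holds in a limited form. The decision to compare depends on the observed outcome, in one direction, with no stated threshold, and in practice it rests with the surgeon-investigator. Separately, an uncontrolled cohort cannot show positive effects of the routine or a transfer of burden to outpatients. The cohort's own descriptive results remain valid, and the primary aim can be met as written.

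The protocol supplies nothing from which to calculate a size. The table shows only how strongly an open threshold matters under assumed inputs; it does not measure a bias in this study. The consequence is for what may be concluded: description is supported and attribution to the routine is not. This is worth correcting but does not invalidate the study. An unseen SAP could add detail, but the conditional rule and the effect wording are fixed in the protocol text.

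**What to change.** 1. **Statistics.** Delete the conditional comparison and the bracketed remark after it. Put in its place: *Adverse events and readmissions at 30 and 90 days, discharge on the day of surgery and additional outpatient appointments will be reported as proportions or counts with 95% confidence intervals for a single uncontrolled cohort, whatever the results. No effect of the routine will be concluded.*
2. **Summary.** Replace the passage on positive effects with a statement that the study will describe these outcomes under the same-day routine.
3. **Secondary aims.** Drop *instead* and ask how many additional outpatient appointments the cohort uses.
4. **Optional.** If a comparison is wanted, specify the comparator now and report it with differences and 95% confidence intervals whatever the results. The same surgeon's later-in-day PKR cases are one candidate. State that they are not randomised, of unknown size and confounded by time of day, and describe their discharge pathway.

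Items 1 to 3 change wording only, and the ethics application is described as still to be made. The price is a more modest conclusion. Item 4 would add record abstraction and coverage of those records in the ethics application, and may give only a wide interval.

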# Objectives

## Primary aims

The primary aims of this 3-month follow-up study to assess safety outcome measures for a same-day PKR surgery protocol, including AE and readmission for any cause.

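### The primary safety outcome is to be reported as a percentage with no interval, so a low or zero event rate in a cohort of unstated size could be over-read

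*Protocol*

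**What the plan says.** Under Primary aims, the protocol sets out "to assess safety outcome measures for a same-day PKR surgery protocol, including AE and readmission for any cause". The 3-month follow-up section gives two windows, 30 days and 90 days, the second listed as "90-day adverse events and/or readmission for any cause". The Summary states what the investigator expects: "The thesis is that the same-day surgery will be both feasible and safe".

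The Statistics section says that "no comparative analyses are planned". A comparison would follow in one circumstance: "Only if unexpected failures will be observed, retrospectively such a comparison will be conducted". On how results will be shown there is a single sentence: "Descriptive data will be presented as unadjusted means with standard deviations, medians with range, or as proportions" (%).

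The cohort comes from one surgeon's list, whose "first morning cases during one consecutive year will be dedicated to a PKR patient". The protocol gives no expected number of patients or operating days. It also gives no confidence interval, precision target or expected event rate.

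**The concern.** The presentation sentence does not name the safety outcome. It is, however, the only rule in the protocol that can apply to it, because no other analysis is planned. It pairs means with standard deviations and medians with ranges, and leaves proportions on their own. If the plan is followed as written, the primary result is a percentage with nothing to show how precisely it was estimated.

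This matters more here than in a study that only describes its patients. The protocol expects to find the routine safe, has no comparator, and leaves N to whatever the surgeon's morning slots yield in a year. In a single-arm study the interval is the main guard against reading too much into a small count. Without it, 0% from 50 patients and 0% from 200 look the same, although they rule out quite different event rates.

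**Working it through.** **Inputs.** The outcome is the proportion of patients with an AE or readmission at 30 or 90 days (Primary aims; 3-month follow-up). The planned presentation is a percentage (Statistics). The protocol gives no N, event rate or precision target, so there is no figure of its own to reproduce. N and the true rates below are assumptions, shown over a range.

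**Formula for zero events.** The exact (Clopper-Pearson) two-sided 95% upper limit for 0/N is 1 − 0.025^(1/N).

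- N = 50: 1 − 0.025^(1/50) = 1 − 0.929 = 7.1%
- N = 100: 1 − 0.025^(1/100) = 1 − 0.964 = 3.6%
- N = 200: 1 − 0.025^(1/200) = 1 − 0.982 = 1.8%

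**Non-zero counts.** AEs of any kind are included, so zero is the extreme case. For x > 0 the limits are beta quantiles: the lower is the 2.5% point of Beta(x, N − x + 1) and the upper is the 97.5% point of Beta(x + 1, N − x).

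| Assumed N | 0 events | 2 events | 5 events |
|---|---|---|---|
| 50 | 0% (0 to 7.1) | 4.0% (0.5 to 13.7) | 10.0% (3.3 to 21.8) |
| 100 | 0% (0 to 3.6) | 2.0% (0.2 to 7.0) | 5.0% (1.6 to 11.3) |
| 200 | 0% (0 to 1.8) | 1.0% (0.1 to 3.6) | 2.5% (0.8 to 5.7) |

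The point is therefore not confined to zero events. At N = 50, two events would appear as 4.0%, while the data would be compatible with anything up to 13.7%.

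**Chance of seeing no event.** This is (1 − p)^N for a true rate p.

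- Assumed p = 2%: 0.98^50 = 36.4%; 0.98^100 = 13.3%; 0.98^200 = 1.8%
- Assumed p = 3%: 0.97^50 = 21.8%
- Assumed p = 5%: 0.95^50 = 7.7%; 0.95^100 = 0.6%

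**An example from the protocol's own Background.** It cites a 25-case series with no AE or readmission over three months, and gives no interval. The upper limit for 0/25 is 1 − 0.025^(1/25) = 13.7%.

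**Discharge on the day of surgery (secondary aim).** The same applies. As an illustration, 45/50 is 90%, with an exact 95% interval of 78.2% to 96.7%.

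**The case against.** The best reply is that intervals are detail that a statistical analysis plan usually supplies. The sentence concerns descriptive data in general, does not say that only these forms will be used, and does not exclude an interval. An unseen plan could add one. Any reader given the counts could also compute it, so nothing would be lost for good.

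Part of this stands. Because an interval can be added at reporting without touching enrolment, data collection or care, the point is not a must-fix. The rest does not dispose of it. The protocol goes beyond silence by stating a form of presentation, and for the type of data that carries the primary aim that form has no measure of uncertainty.

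A reader might also infer more than the documents support:

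- **That a 0% rate would be published as proof of safety.** No such rule is written. The aim is to assess, and the Summary's thesis is an expectation. Over-reading is a risk only.
- **That every result is fixed as a bare percentage.** The same sentence also provides means with standard deviations and medians with ranges.
- **That the cohort will be small because there is one slot a day, or that events will be rare.** Neither the number of operating days nor an event rate is given, and the outcome is not limited to serious events.
- **That the study fails for want of an expected N or a pass/fail threshold.** Both would be useful, but they are separate, secondary matters, and the case for an interval does not need them.

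**Conclusion.** The point holds as a recommendation on reporting and inference. The protocol's only presentation rule gives its primary safety proportions no interval, in a single-arm study that expects to conclude that the routine is safe.

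How much this matters depends on N, which has to be assumed. With zero events the data could not exclude a rate of up to 7.1% at N = 50 or 3.6% at N = 100. At N = 200 the limit is 1.8% and the problem is modest. The absence of any stated uncertainty for the primary outcome holds at every N. Only its consequence shrinks as N grows.

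**What to change.** Add to the Statistics section, after the presentation sentence:

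*The proportions of patients with an adverse event and with a readmission, each at 30 and at 90 days, and the proportion discharged on the day of surgery, will be reported as n/N with exact (Clopper-Pearson) two-sided 95% confidence intervals. Any statement on safety will cite the upper confidence limit and not only the point estimate.*

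The cost is two sentences and a trivial amount of analysis. No extra patients or data are needed, and care is unchanged. The one real downside for the investigator is that the safety statement will look less favourable than a bare percentage. Optionally, the section could also state the number of patients expected from the morning slots and the upper limit that this number gives with zero events.

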## Ethical considerations

### Ethics approval

Approval from the Swedish Ethical Review Authority will be applied for.

### Conventional X-ray

No additional radiological examinations will be performed to the ordinary routine.

# Administrative procedures

## Data management

The clinical investigator will be responsible for the compilation and statistical treatment of data.

## Reports and publication of results

It is anticipated that the results of this study will be published in an international journal of orthopaedics. In this context the results of the study are owned solely by the clinical investigator, who decides on the final form of the report.

## Timeline

All the data collection, the statistical analysis and writing the manuscript is anticipated to be done within one year from study start (2020).

## Study centres

All the operations will be performed at Trelleborg hospital, a public hospital within the general health care system of Region Skåne.

## Surgeons

One single high-volume surgeon will be performing all the operations.

## Conflicts of interest

None

## Disclosures

The investigator (surgeon) has no relevant financial or nonfinancial relationships related to the study.

